### Data Collection and Patients’ Follow‐Up

Three follow‐up visits are planned for each patient. Visit 1 (i.e., Day 1 of treatment) will include a measurement of quality of life using the ICIQ‐UI‐SF and KIDSCREEN‐10 questionnaires, a clinical examination, and an evaluation of the voiding diary completed over a 72‐h period before the visit. The treatment kit assigned by the centralised randomisation system will be given to the patient to cover the 4 weeks of treatment, and the first administration will be performed by a nurse, after a therapeutic education session. Each patient will receive a treatment journal to record the information needed to monitor compliance (dates and times of administration, observations), as well as adverse effects. If the patient is a child, parents will be asked to complete the document.

Visit 2 will take place after 2 weeks of treatment. It will include a clinical examination and an evaluation of the voiding diary and treatment journal.

Visit 3 will take place at the end of the 4 weeks of treatment. It will include a clinical examination and an evaluation of the voiding diary and treatment journal. If the patient has already discontinued the treatment before the visit, the date of discontinuation will be noted. Otherwise, the treatment will be interrupted on this visit. A cystomanometry will be carried out under the same conditions as the one carried out before the inclusion visit, as well as a renal ultrasound. Quality of life and usability of the product will be assessed.

A urine pregnancy test will be performed at each visit in female patients of childbearing age.

Between visits, patients will be asked to record the number and volume of catheterisations, as well as urine leakage for 72 consecutive hours in their voiding diary provided during the inclusion visit (Data S3).

Treatment or placebo may be stopped prematurely at any time in case of serious adverse effect, if the investigator deems it necessary for the patient's safety, or if the patient wishes to discontinue treatment. In this case, only the next scheduled visit is maintained (i.e., Visit 2 or 3) and the procedures planned for Visit 3 will be carried out to collect outcomes. The patient will continue to receive usual medical care.

A follow‐up call will be scheduled 7 days after the last consultation, to assess any residual effect of the treatment or placebo.

### Data Management and Monitoring

During the trial, the investigator, or any person designated in writing in the task delegation form, will document an electronic case report form (eCRF) for each patient included in the study. The eCRF will be set up and managed by the Nancy Centre Hospitalier Régional Universitaire (CHRU). The investigator will be responsible for the quality, accuracy and relevance of the data collected in the eCRF.

Identification of included patients will be limited to an identification code assigned on inclusion composed as follows: Centre number – Inclusion number in chronological order.

Compliance with the clinical investigation plan and security regulations, as well as data accuracy, will be monitored by the Clinical Research Associate mandated by the sponsor (Nancy CHRU). The full database will be stored on the Nancy CHRU server for 15 years after the end of the trial. An audit could be conducted at any time by independent experts on the sponsor demand.

### Safety Profile

All patients included in the study will have already received oral anticholinergic treatment, which reduces the risk of allergy to oxybutynin. In addition, any contraindication to the use of oral anticholinergic treatment also contraindicates participation in the present study, which should reduce the risk of serious AEs (SAEs).

Intravesical administration is associated with better bioavailability of oxybutynin compared to oral administration, as there is no first intestinal passage. This results in a reduction of its main metabolite, N‐desethyloxybutynin, which is less effective and has significant side effects [24]. Previous studies showed that the occurrence of adverse effects was lower with intravesical administration, as compared with oral oxybutynin [11, 15, 25, 26, 27, 28]. In the study by Schröder et al. [11], the adverse effects specifically found in the IVO group were: pain at the instillation site, headaches, abdominal pain, urinary urgency, decreased sweating, and hypotension. The adverse effects found in both modes of administration of oxybutynin were: dry mouth, constipation, dizziness, fatigue, dry eyes, attention disorders, drowsiness, apathy, and delayed urination. Finally, the expected risks of intravesical instillation, both for the oxybutynin and placebo groups are as follows: pain at the instillation site, urinary urgency and UTI.

Adverse effects will be systematically documented at each visit using the treatment journal. In case of fever, the patient will be prescribed an emergency urine culture. If positive, the patient will be urgently referred to a doctor at his/her centre to assess the need for antibiotics.

In our study population, where the next therapeutic step is often intradetrusor injections of onabotulinumtoxinA (an invasive procedure requiring anaesthesia), we considered placebo as the most appropriate comparator to establish the true effect size of IVO beyond natural variability. The 4‐week treatment period was chosen as a compromise to provide sufficient time to assess efficacy while avoiding unnecessarily long exposure to an ineffective treatment. All participants will continue to receive standard conservative management during this period, including intermittent catheterisation and surveillance. Investigators may request unblinding at any time in the event of a severe medical emergency potentially related to the study drug. Isolated incontinence episodes will not in themselves be considered a medical emergency requiring unblinding, as they are expected in children who have previously failed or not tolerated oral anticholinergics.

The unblinding procedure will be managed by the Lyon Hospitals Poison Control Centre (Centre Anti‐Poison [CAP]), which will provide access to information on the treatment of participants in the event of a medical emergency. The investigator may request unblinding for any reason deemed essential to the therapeutic management of the patient, by contacting the CAP. Any emergency unblinding must be followed by a SAE report.

There is no evidence in the literature suggesting any additional risk beyond the study period. Repeated IVO should not result in an accumulation of oxybutynin in the body, as its elimination half‐life is short (2 h). However, patients and their parents will be asked to report any suspected delayed events to the investigator, and a follow‐up call will be scheduled 7 days after the last consultation, to ensure that there are no residual effects of the treatment. As patients with a neurogenic bladder are systematically monitored as part of their pathology follow‐up, any delayed adverse effects will be identified by the investigators.

An independent Data and Safety Monitoring Board (DSMB), composed of two paediatric surgeons and one biostatistician, will be responsible for overseeing the trial and addressing any safety concerns that may arise.

### Sample Size

Schröder et al. [11] found a 32% increase in maximum bladder capacity in adults using IVO compared with baseline values (*P* < 0.001). In our target population, Raes et al. [29] found a 33% increase in maximum bladder capacity when treated with tolterodine. As patients included in our study already use catheterisation, there is no reason to expect a strong placebo effect from instillation. Given the lack of precise data on the effect of IVO in our target population and based on experts’ opinion, we expect a 33% increase in maximum bladder capacity in the treated group, a 5% increase in the placebo group, a mean (SD) initial bladder capacity of 170 (80) mL, and a correlation between measurements for the same patient of 0.8. To obtain a power of 0.9 with a type I error risk set at 0.05, 26 patients per group are needed. To allow for a margin of error, we rounded up the total expected sample size to 60.

### Statistical Analyses

For the primary outcome, an intention‐to‐treat analysis will be conducted to assess the difference between the two groups in the evolution of maximum bladder capacity, using a linear mixed model accounting for repeated measurement, age stratification, and treatment exposure as a binary variable. A secondary exploratory analysis will be conducted to account for any imbalance that may occur between groups despite randomisation due to the small sample size. Multivariate linear regression will be performed, adjusted for age and gender.

Given the small sample size and the short duration of follow‐up for each patient, there should be little or no missing data. For the primary outcome, patients lost to follow‐up will be assigned the value measured during the last cystomanometry performed (i.e., last observation carried forward).

No intermediate analysis is planned given the small sample size.

Two secondary outcomes will be analysed following a fixed sequence in a priori ordered hypotheses:
Maximum bladder pressure after 4 weeks of treatment: the two groups will be compared using the same methodology as for the primary outcome;Time to treatment failure: the two groups will be compared using a two‐tailed log‐rank test. If a patient is lost to follow‐up, the date of treatment failure will be the date of last news plus 1 day.

Occurrence of AEs will be compared in the two groups using a Fisher's test with a significance threshold = 0.05.

The proportions of responders and continent patients after 4 weeks of treatment will be calculated with their 95% CI.

Standardised differences in patients’ quality of life assessed with the KIDSCREEN‐10 and ICIQ‐UI‐SF questionnaires will be compared between the two groups using a Wilcoxon test, with a significance threshold = 0.05. As recommended by the KIDSCREEN‐10 developers, an additional subgroup analysis will be performed to distinguish children aged 6–7 years from those aged 8–17 years.

Changes in voiding diary elements, urodynamic parameters, and renal ultrasound parameters after 4 weeks of treatment will be compared using a Wilcoxon test, with a significance threshold = 0.05.

Product usability will be assessed using the linear transformation of the UMUX‐LITE score proposed by the authors and comparing the average scores in both groups to reference scores (e.g., a score >80 is associated with good usability). A median score will be calculated in the two groups for the supplementary usability questions specific to our study.

Finally, the association between responder status and the following variables will be tested using a Fisher's test, with a significance level = 0.05:
Cause of discontinuation of oral anticholinergic treatment (inability to swallow, no effect on bladder hyperactivity, intolerable side effects);Neurological status (walking vs non‐walking, presence of a ventriculoperitoneal shunt valve);Concomitant diseases;Concomitant treatment.

All analyses will be conducted with R statistical software, version 4.0.3 (R Foundation for Statistical Computing, Vienna, Austria).

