### Endpoints

The primary outcome is change in maximum bladder capacity after 4 weeks of treatment (end of follow‐up). This parameter is considered by experts to be an objective marker of improvement in neurogenic bladder. It will be measured by cystomanometry and is defined by the maximum bladder volume (mL) recorded after filling via the urethral catheter, which may occur under one of the following conditions: (i) when the patient is given permission to urinate, (ii) when detrusor pressure reaches 40 cmH₂O, (iii) when the expected maximal bladder volume for age is reached, or (iv) when the patient reports an irrepressible urge to urinate. In younger patients, urination occurs spontaneously, and this value will be obtained *a posteriori* by curve analysis. Change will be assessed between two measurement times: one before initiation of treatment, performed <6 months prior (i.e., reference cystomanometry), at best in the absence of oral anticholinergic treatment, and the other at the end of treatment, under the same conditions. Cystomanometers will be calibrated at the start of each procedure.

Secondary outcomes will be:
The 4‐week change in maximum bladder pressure, measured by cystomanometry.Time to treatment failure within 28 days, defined on the basis of criteria available in the literature (at least one of three criteria):
Treatment deemed ineffective by the patient or practitioner;A <50% reduction of incontinence episodes reported in the voiding diary;Intolerable side effects reported by the patient.

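### With only one planned test after baseline, last observation carried forward for the primary outcome becomes baseline carried forward and imputes a change of exactly 0 mL

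*Protocol article*

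**What the plan says.** All references are to the Protocol article.

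- **Statistical Analyses.** The primary analysis is by intention to treat, with a linear mixed model for repeated measurements. The section expects hardly any missing data. It then fixes a rule for the primary outcome: children lost to follow-up "will be assigned the value measured during the last cystomanometry performed", named as last observation carried forward. Maximum bladder pressure, the first of the two ordered secondary outcomes, is analysed in the same way.
- **Endpoints.** "Change will be assessed between two measurement times: one before initiation of treatment, performed <6 months prior". The second measurement is at the end of treatment. The reference test should ideally, but need not, be done off oral anticholinergics.
- **Data Collection and Patients' Follow-Up.** For Visit 2, at two weeks: "It will include a clinical examination and an evaluation of the voiding diary and treatment journal". No cystomanometry is planned then for a child still on treatment. For Visit 3, at four weeks: "A cystomanometry will be carried out under the same conditions as the one carried out before the inclusion visit". If treatment stops early, only the next scheduled visit is kept, and there "the procedures planned for Visit 3 will be carried out to collect outcomes".
- **Sample Size.** The calculation gives 26 per group. "To allow for a margin of error, we rounded up the total expected sample size to 60".

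**The concern.** Carrying the last observation forward normally presupposes an intermediate value after the start of treatment. Here none is planned. If a child has no end-of-treatment test, the last cystomanometry on file is the reference test, and follow-up minus baseline is 0 mL by construction. The label does not tell the reader this.

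The size of the treatment effect is at stake. The plan expects capacity to rise by 33% on IVO and by 5% on placebo, so adding zeros moves the estimated difference by an amount that depends on how many children each arm loses. The carried value may also be months old and may have been recorded on an oral anticholinergic that the Population and Sampling section stops at inclusion. In that case no change is not necessarily a cautious guess.

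**Working it through.** **Inputs (Sample Size section).** Baseline mean 170 mL, SD 80 mL; gains of 33% and 5%; correlation 0.8; power 0.90; type I error 0.05 (sidedness not stated, two-sided assumed); 60 children at 1:1, so 30 per arm.

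**Step 1: the plan's own figure.**
- Expected gains: 0.33 × 170 = 56.1 mL and 0.05 × 170 = 8.5 mL. Difference: 47.6 mL.
- SD of change: 80 × √(2 × (1 − 0.8)) = 50.6 mL.
- A two-sample comparison of change needs 24 per group (normal approximation) or 25 (t-test). The stated 26 is reproduced to within two.

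**Step 2: expected difference under the rule.** Let a and b be the proportions lost without a second test on IVO and placebo. With loss at random and every lost child given 0 mL:

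expected difference = (1 − a) × 56.1 − (1 − b) × 8.5

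With equal loss d this is 47.6 × (1 − d). The protocol gives no loss rate, so the rates below are assumptions. The 13.3% is 8/60, the distance from 52 to 60. Power was simulated with 30 per arm, a t-test on change and 40,000 replicates. The observed-only column stands in for the mixed model without imputation, whose expected difference stays at 47.6 mL.

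| Loss, IVO / placebo | Difference, carried forward (mL) | Relative to 47.6 | Power, carried forward | Power, observed only |
|---|---|---|---|---|
| 0 / 0 | 47.6 | 0 | 0.948 | 0.948 |
| 5% / 5% | 45.2 | −5% | not run | not run |
| 10% / 10% | 42.8 | −10% | 0.917 | 0.923 |
| 13.3% / 13.3% | 41.3 | −13% | 0.908 | 0.917 |
| 20% / 20% | 38.1 | −20% | 0.873 | 0.890 |
| 20% / 6.7% | 36.9 | −22% | 0.824 | 0.914 |
| 6.7% / 20% | 45.6 | −4% | 0.953 | 0.912 |
| 0 / 13.3% | 48.7 | +2% | not run | not run |

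Example, 20% / 6.7%: 0.80 × 56.1 − (28/30) × 8.5 = 44.88 − 7.93 = 36.9 mL.

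**Step 3: standard error.** The variance of change is 50.6² = 2560. Under the rule, the variance in an arm with loss p and mean gain m is (1 − p) × 2560 + p(1 − p) × m². At 13.3% loss per arm:
- IVO: 0.867 × 2560 + 0.1156 × 56.1² ≈ 2582.
- Placebo: 0.867 × 2560 + 0.1156 × 8.5² ≈ 2227.
- SE = √((2582 + 2227)/30) = 12.7 mL. With observed values only, SE = √(2 × 2560/26) = 14.0 mL.

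**Step 4: no treatment effect.** With 13.3% loss per arm and a common gain of 8.5 mL, simulated type I error is 0.048. With 20% / 6.7% loss and the same common gain, the expected bias is 0.80 × 8.5 − (28/30) × 8.5 = −1.1 mL and type I error is 0.051.

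If capacity instead falls in both arms once oral anticholinergics are stopped, the zeros flatter the arm with more loss. With assumed common falls of 20 and 40 mL and 20% / 6.7% loss, the bias is (28/30 − 0.80) × 20 = 2.7 mL and (28/30 − 0.80) × 40 = 5.3 mL towards IVO. Type I error is about 0.053 and 0.060.

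**The case against.** The best defence is that the rule will rarely be used. Follow-up lasts four weeks, the protocol expects hardly any missing data, and the Visit 3 procedures are brought forward for a child who stops early. Such a child keeps a real post-baseline value by attending the next visit. The step from 52 to 60 is called a margin of error, not a dropout allowance, so 13.3% is only a convenient reference point. At 5% loss per arm the shift is 2.4 mL, against an SE of about 13 mL. All of this stands, and it limits the size of the problem.

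Three stronger readings are tempting, and the documents do not support them.

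- **That zero is wrong in both arms.** This assumes that a lost child would have changed like those who stayed, which is missing at random and not a fact. Imputing lost children from the placebo arm gives (1 − a) × 56.1 + a × 8.5 − 8.5 = 47.6 × (1 − a). At 13.3% that is also 41.3 mL, and at 20% on IVO it is 38.1 mL, against 36.9 mL under the rule. Much of the shift is therefore a difference between assumptions about the lost children.
- **That the standard error is too small.** The 12.7 mL is the true sampling SE of the carried-forward contrast under random loss, because the formula includes the spread between the zeros and the observed values. It is smaller than 14.0 mL because it belongs to a different quantity. Type I error does not rise with equal loss.
- **That data are invented.** The rule is a disclosed, prespecified single imputation.

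The defence does not supply a reason to keep the rule. If almost nobody is lost it brings no benefit, and if children are lost it moves the estimate. The possibly on-drug reference test affects every child's change score and is a separate point. It matters here only because it means that zero change is not always conservative.

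**Conclusion.** The point holds as a should-fix. For a child with no second cystomanometry, the stated rule is baseline carried forward with a change of exactly 0 mL, and the planned model makes it unnecessary.

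Under the plan's effect assumptions and missing at random, the rule mostly pulls the estimate towards no effect: by about 5% at 5% equal loss, 13% at 13.3%, and 22% at 20% on IVO against 6.7% on placebo. Power stays above 0.90 up to 13.3% equal loss. The rule can favour the arm with more loss if capacity falls after oral anticholinergics are stopped, but that needs both unequal loss and a fall that the documents do not quantify.

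A reader might infer that the primary test is invalid. The calculations do not show that: type I error stays near 0.05 with equal loss and reaches only about 0.06 in the most extreme case examined. The weakness lies in the effect estimate and in a label that hides what is imputed.

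**What to change.** Delete the carried-forward sentence from the primary analysis, and state that it does not apply to maximum bladder pressure either. Fit the planned likelihood-based mixed model to all observed values of all randomised children, including those with only a baseline value and those whose end-of-treatment procedures were brought forward. State that this analysis rests on missing at random. If baseline carried forward or a reference-based imputation from the placebo arm is wanted, keep it as a labelled sensitivity analysis and call it by its proper name.

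The cost is a change of wording, a few lines of code, and a slightly larger SE if children are lost (14.0 against 12.7 mL at an assumed 13.3% per arm). The change should be made before unblinding, so that it cannot appear driven by the data.

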### Objectives

The main objective of the POXIPEN trial is to assess the efficacy of IVO vs placebo on maximal bladder capacity in children with neurogenic bladder secondary to myelomeningocele (spina bifida), performing intermittent catheterisation, and for whom oral anticholinergic therapy has been deemed ineffective or associated with adverse effects.

Secondary objectives are:
To assess evolution of maximum bladder pressure after IVO (or placebo);To assess incontinence (i.e., time to clinical failure of treatment as perceived by the patient) after IVO (or placebo);To describe treatment tolerance and adverse effects;To assess the number of responders and continent patients after IVO (or placebo);To assess usability of IVO;To assess changes in patients’ quality of life after IVO (or placebo);To describe changes in patients’ voiding diary data after IVO (or placebo);To describe changes in urodynamic and in renal ultrasound parameters after IVO (or placebo);To identify patients’ characteristics associated with a greater likelihood of responding to IVO.

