Occurrence of adverse events (AEs; including digestive, psychiatric, neurological, skin, urological and pain‐related disorders) and their time of onset, as recorded by the patient in his/her treatment journal (Data S1) or by the practitioner during follow‐up visits.Proportion of responders, i.e., patients who had a ≥50% reduction in urinary incontinence episodes recorded in their voiding diary [20], after 4 weeks of treatment, with no intolerable AEs.Proportion of continent patients, i.e., patients who had a 100% reduction in urinary incontinence episodes, after 4 weeks of treatment [20].Standardised difference in patient's quality of life, as assessed by changes in the International Consultation on Incontinence Questionnaire‐Urinary Incontinence Short Form (ICIQ‐UI‐SF) [21] and the 10‐item KIDSCREEN questionnaire (KIDSCREEN‐10) [22] scores between the inclusion visit and the end of follow‐up.Changes in voiding diary parameters, as assessed by the change in the number and volume of urinary catheterisations over 72 h during the week preceding each follow‐up visit. If treatment is effective, voided volume should increase.Changes in urodynamic parameters between the reference cystomanometry and the cystomanometry performed at the end of treatment:
Bladder compliance (mL/cmH_2_O),Minimum filling volume causing uninhibited detrusor contraction,Detrusor leak point pressure (cm H_2_O),Volume of bladder filling during urine loss (mL).

To ensure consistency and standardisation across centres, all participating investigators will be asked to perform both cystomanometries under the same conditions for each patient, regarding bladder filling rates and patient positioning.
Changes in renal ultrasound parameters between the reference renal ultrasound (performed <2 months prior to treatment initiation), and the one performed at the end of treatment:
Pyelon anteroposterior diameter (mm),Ureter diameter (mm).

If treatment is effective, a reduction in both diameters could be observed, as a result of the decrease of pressure in the renal system.
Usability of the product, measured by the Usability Metric for User eXperience (UMUX)‐LITE scale [23] coupled with seven ad hoc questions specific to the treatment and disease under study, measured on a 7‐point Likert scale (from strongly disagree to strongly agree; Data S2).

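### Time to treatment failure: the diary criterion has no stated visit and can contradict responder status, loss counted as failure can bias the log-rank test if loss is unequal, and no age stratification is named

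*Protocol article*

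**What the plan says.** - **Protocol, Objectives.** The aim is described as "time to clinical failure of treatment as perceived by the patient".
- **Protocol, Endpoints.** The outcome is "Time to treatment failure within 28 days", met by "at least one of three criteria": "Treatment deemed ineffective by the patient or practitioner"; "A <50% reduction of incontinence episodes reported in the voiding diary"; and "Intolerable side effects reported by the patient". No time point is attached to the diary criterion.
- **Protocol, Endpoints (responders).** A responder has at least a 50% reduction in diary episodes after 4 weeks, with no intolerable adverse event.
- **Protocol, Endpoints and Data Collection.** Diary parameters are taken "over 72 h during the week preceding each" follow-up visit. On treatment these are Visit 2 (2 weeks) and Visit 3 (4 weeks). Onset times of adverse events and the date of early discontinuation are also recorded.
- **Protocol, Population and Sampling.** Randomisation is 1:1, stratified by age (6–11 and 12 years or older).
- **Protocol, Statistical Analyses.** The primary model accounts for the age strata. Time to failure is second in the fixed sequence and is compared by a two-tailed log-rank test, with no stratification mentioned. For a child lost to follow-up, "the date of treatment failure will be the date of last news plus 1 day". Little or no missing data is expected, and no drop-out rate is given.

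**The concern.** Four features of this endpoint are fixed in a way that can mislead.

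1. The failure and responder definitions use the same 50% threshold, but only the responder definition names a time. One child can therefore be reported as having failed and as having responded.
2. Diary failures can be seen only around days 14 and 28, while the other criteria can be dated to the day. The endpoint mixes the two without saying how diary failures are dated.
3. Loss to follow-up enters as an event. If one arm loses more children, the difference in loss is read as a difference in failure. Each lost child is 1/30 = 3.3 percentage points of an arm.
4. The test as named ignores the factor used to stratify randomisation, although the primary analysis respects it.

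The objective also speaks of patient perception, whereas the definition admits the practitioner's judgement and a diary rule. At stake is how one of the two hierarchically tested secondary results is read. The primary outcome is not affected.

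**Working it through.** The protocol states no event rate, power or drop-out rate for this endpoint, so there is no figure to reproduce. All rates below are assumptions, shown as ranges.

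**1. Can a child be both failure and responder?** Take at most half the baseline count at Visit 3 with no intolerable adverse event (responder) and more than half at Visit 2 (diary criterion met). Nothing in the two definitions excludes this child. A second route is a child with at least a 50% reduction whose treatment is judged ineffective.

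Size of the first route: let the baseline 72-hour count be B ~ Poisson(m), excluding B = 0, and each on-treatment count Poisson(m(1 − r)), independent given B, with a stable true reduction r. With q(B) = P(count ≤ B/2), averaged over B:

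- responder at Visit 3 = E[q]
- failure at either visit = 1 − E[q²]
- both = E[q(1 − q)]

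For m = 6 and r = 60%: 68% responders, 49% failures, 17% both. Percentage who are both, over a range:

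| True reduction | m = 6 | m = 12 | m = 20 |
|---|---|---|---|
| 40% | 19.8 | 19.0 | 18.0 |
| 50% | 19.4 | 19.5 | 19.5 |
| 60% | 17.1 | 16.3 | 15.3 |
| 70% | 12.9 | 10.3 | 7.5 |
| 80% | 7.6 | 4.1 | 1.8 |

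The overlap is largest when the true reduction is near or somewhat below the threshold, and small when the effect is strong and counts are high.

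**2. What the loss rule does to the failure proportion.** If a proportion p is lost, observed failure = (1 − p) × true failure + p. Assume true failure of 60% on placebo and 30% on IVO (30 points).

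- 4 of 30 lost per arm (p = 0.133): 0.867 × 60 + 13.3 = 65%; 0.867 × 30 + 13.3 = 39%. Difference 26 points.
- 2 of 30 lost on placebo, 6 of 30 on IVO: 0.933 × 60 + 6.7 = 63%; 0.8 × 30 + 20 = 44%. Difference 19 points.

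**3. What it does to the log-rank test.** Simulation with 30 per arm and 2,000 runs per scenario: diary failures at days 14 and 28, other failures and losses spread evenly over follow-up, loss unrelated to outcome. Monte Carlo standard error at 5% is √(0.05 × 0.95/2000) = 0.5 points.

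No treatment effect. Higher failure rates: 40% at day 14, 30% of the rest at day 28, 10% at other times. Lower: 20%, 15% and 5%. Type I error with loss counted as failure:

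| Loss, placebo/IVO | Higher rates | Lower rates |
|---|---|---|
| 0/0% | 5.0% | 4.9% |
| 5/5% | 5.5% | not run |
| 10/10% | 5.1% | not run |
| 0/10% | 7.0% | 9.0% |
| 5/15% | 7.6% | 8.1% |
| 0/20% | 14.6% | 20.0% |

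The excess rejections go against the arm that loses more children. With lost children censored at last contact, type I error was 4.0% to 5.4% throughout.

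Assumed benefit (diary failure at day 14 of 60% versus 25%, then 40% versus 20% at day 28, with 10% failing at other times in each arm):

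| Loss, placebo/IVO | Power, loss = failure |
|---|---|
| 0/0% | 77% |
| 10/10% | 66% |
| 0/10% | 54% |
| 5/15% | 47% |
| 0/20% | 30% |
| 15/5% | 80% |
| 20/0% | 91% |

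Censoring gave 72% to 75% in all of these. The simulated loss was independent of outcome, which favours censoring.

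**The case against.** Several stronger readings are tempting, and the document does not support them.

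- **That the endpoint does not measure time.** Two of the three criteria can be met on any day, and adverse-event onset and discontinuation dates are recorded. Only the diary component is confined to two assessment points. Both arms share the same blinded visit schedule, and ties at two dates do not invalidate the test: simulated type I error was 5.0% without loss.
- **That every child is already a failure at the start.** The criterion cannot be evaluated before Visit 2, so no child meets it on Day 1.
- **That drop-out drives the result.** The protocol expects little or none, gives no rate, and keeps the next scheduled visit, with the Visit 3 procedures, for children who stop early. Stopping treatment is therefore not loss. Equal loss leaves type I error at about 5%.

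Counting loss as failure is also a recognised composite convention. Censoring has its own weakness, because families may leave when treatment is not working. The unstratified log-rank test is a valid test, and strata or sensitivity analyses may be in a statistical analysis plan that is not shown. The outcome is last in the sequence, so nothing is tested after it.

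What remains is the conflict between the failure and responder definitions, the conditional bias under unequal loss, a named test that omits the stratification factor, and the mismatch between objective and endpoint.

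**Conclusion.** The point holds in a limited form. The definitional conflict follows from the text alone. Its size, about 2% to 20% of children, depends on the assumed Poisson counts (baseline means of 6 to 20) and true reductions of 40% to 80%. The loss rule is a conditional risk: it needs appreciable, unequal loss, and its direction depends on which arm loses more. Under the assumed failure rates, type I error rises to about 7–9% at 0/10% loss and 15–20% at 0/20%; equal loss costs power only. The missing age stratification is a smaller matter of consistency with the design and the primary model. The point merits correction before unblinding, and the primary analysis and the sample size are untouched.

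**What to change.** 1. Name a log-rank test stratified by age group (6–11, 12 years or older).
2. State at which visit or visits the diary criterion is judged, and reconcile this with the responder definition so that the status of a child who crosses 50% between visits is unambiguous.
3. Treat diary failures as events in a visit interval (discrete-time or interval-censored model), at least as a supporting analysis.
4. Beside the lost-as-failure rule, report an analysis that censors lost children at last contact, and give the number lost per arm.
5. Align the objective's patient-perceived wording with the three-criterion definition.

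Replacing the outcome with a yes/no failure at Day 28 is not needed. It would largely duplicate the responder endpoint and give up the stated time objective.

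Cost: wording and slightly more analysis, with no extra patients, visits or data. In the visit-interval analysis the diary component has no day-level timing, which the diary schedule does not supply in any case.
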